### Participants and procedure

#### Inclusion and exclusion criteria

We will include outpatients [1] aged 18–65 years [2] with a main diagnosis of non-psychotic non-chronic (<2 years) major depressive episode (DSM-IV criteria) of moderate to severe intensity (Montgomery Asberg Depression Scale score >24) [49] taking at least one antidepressant [4] able to speak, read and understand French [5] and able to give written informed consent.

We will exclude subjects [1] with a current diagnosis of substance abuse or dependence in the 6 months prior to inclusion, excluding tobacco, [2] current psychotic features, [49] duration of current depressive episode >2 years, [4] current organic mental disorder or mental retardation, or severe comorbid medical condition, [5] lifetime history of schizophrenia, or schizoaffective or bipolar disorder, manic, hypomanic, or mixed episodes according to DSM-IV criteria, [6] sensory or cognitive disabilities, [7] hospitalized full-time at the time of inclusion, [8] having a relationship or being employed by the sponsor or investigator. We will also exclude patients who are planning a long stay outside the region preventing compliance with the scheduled visits, and subjects participating in another trial.

#### Recruitment

Participants will be recruited via medical consultations in the 11 French investigation centers.

Written informed consent will be obtained from participants.

#### Eligibility assessment and randomization

People who apply for participation in the study will receive an information letter with comprehensive details on study procedures. Signed written informed consent will be obtained from all participants. They will be informed that they can withdraw from the intervention and/or study at any time without any negative consequences.

The first visit will consist in evaluating the following data:○ Sociodemographic characteristics: age, gender, nationality, marital status, educational level, employment status;○ Psychopathology using the Mini-International Neuropsychiatric Interview (M.I.N.I.) [50];○ Number of previous depressive episodes, date of onset of the current episode;○ Depression intensity using the Montgomery Asberg Depression Scale (MADRS) and Beck Depression Inventory (BDI);○ Global functioning using the Functioning Assessment Short Test (FAST);○ Quality of life using the World Health Organization Quality Of Life measure-26 (WHOQOL-26) scale;○ History of psychotropic treatment (name, dose);○ Treatment adherence using the Medication Adherence Rating Scale (MARS);○ Lifetime suicidality using the Columbia–Suicide Severity Rating Scale (C-SSRS).

All inclusion and non-inclusion criteria will be checked by the study investigator. Patients will then be informed of their eligibility and randomized with the Capture Software System (Clinsight). Randomization will be performed with a permuted-block 1:1 ratio randomization list with varying block sizes and will be stratified in participating centers. Allocation concealment will be achieved by a centralized randomization procedure via an electronic case-report form.

#### Assessments

Patients will be assessed by clinicians blinded to treatment allocation, at inclusion (1–3 weeks before the intervention: visit 1) and at 3 months (end of the psychoeducational program: visit 2), 6 months (visit 3), 9 months (visit 4) and 15 months (visit 5) after inclusion. Patients will be advised to refrain from telling which group they were allocated to during visits.

See Fig. 1 for a detailed overview.

**Fig. 1 Fig1:**
[figure not shown]
Study flow

Investigators should make every effort to minimize the number of patients lost to follow-up and obtain a maximum of information on patients lost to follow-up, particularly in looking for any adverse events.

To limit patients lost to the touch, participants in the intervention group will be sent a text message on their mobile phone (internet-based free site) one day before each psychoeducational session. Each participant will receive two text messages: one the week before and the other the day prior to each follow-up visit.

## Intervention

### ENVIE: the first French psychoeducational group program

#### Add-on psychoeducational group program

The intervention will consist of 9 weekly, 90-min sessions led by two trained educators (nurse and medical doctor). Each group will consist of 8–10 participants. The ENVIE program will provide participants with the latest medical knowledge on depression and effective treatments in a didactic manner [51–57], as well as the latest innovating psychological skills to cope with depressive symptoms and maintain motivation in behavioral activation [39, 40, 58]. These psychological skills belong to Acceptance and Commitment Therapy [58].

The program includes 9 sessions, each focusing on a specific theme or skill:Presentation of the program and the matrix, and psychotherapeutic tools used during the entire program to motivate patients to behave in a manner that is consistent with what is important in their life [58].Functional analysis of depression using the matrix (patients are taught to understand which symptoms/behaviors are linked to depression, why they feel they are struggling, and what they can do to stop the struggle)Causes leading to depressionConsequences of depression and comorbiditiesNeurobiological bases of depressionSelf-analysis of mood state, recognition of prodromal symptoms of relapseInformation about antidepressants, and evidence-based medical treatments for unipolar depressionLifestyle recommendationsBehavioral activation skills

During sessions, participants will be encouraged to raise questions about anything they want to know about depression. To enhance the active role of patients, each session will be followed with take-home homework.

One or two psychoeducational groups of 8 to 10 patients will be planned in each center.

#### Treatment as usual

Treatment as usual will consist of the usual clinical management of depression including psychiatric evaluation and adaptation of pharmacological treatment. There will be no treatment restriction during the study period. The current pharmacological treatment will be recorded at each visit.

## Endpoints

### Safety endpoints

Incidence, relatedness, and severity of treatment-emergent adverse events will be evaluated at each visit until the end of study. Safety parameters assessed in this clinical trial will be recorded and evaluated through repeated clinical examinations of the patients. It relies on assessment of suicidality using the Columbia–Suicide Severity Rating Scale (C-SSRS) [59]: rate of suicidal behaviors (completed suicide and suicide attempts) at 15 months post inclusion, variation of severity and intensity of suicidal ideations subscores between baseline and at 3, 6, 9 and 15 months after inclusion. If a patient exhibits a high-risk of suicide (increased suicide ideations, planning a suicide attempt) during a visit, investigators will contact the psychiatrist in charge of this patient.

Moreover, acceptability will be assessed. It will consist in the number of missed sessions, and satisfaction at 3 months post inclusion using a Likert scale ranging from 0 (not useful at all) to 10 (extremely useful) for the intervention group.

### Efficacy endpoints

#### Primary endpoint

Remission rate of the index episode at 15 months after inclusion, defined by a Montgomery and Asberg Depression Rating Scale (MADRS) [60] score ≤ 12 for over 8-weeks, without relapse during the follow-up period.

#### Secondary endpoints

Variation of the depression intensity between baseline, and at 3, 6, 9 and 15 months after inclusion using MADRS and Beck Depression Inventory (BDI) [60, 61];Evolution of MADRS and BDI scores during follow-up;Response rate (50 % decrease in MADRS score) at 15 months after inclusion;Relapse rate (MADRS >12 after remission of the index episode) at 15 months after inclusion;Hospitalization rate during follow-up;Variation of global functioning, using the Functioning Assessment Short Test (FAST) [62], between baseline, and at 9 and 15 months after inclusion;Variation of quality of life using the World Health Organization Quality Of Life measure-26 (WHOQOL-26) scale [63] between baseline, and at 9 and 15 months after inclusion;Variation of treatment adherence using the Medication Adherence Rating Scale (MARS) [64] between baseline and 15 months after inclusion;Variation of benzodiazepines doses between baseline and at15 months after inclusion;Discontinuation rate of the antidepressant treatment at 15 months after inclusion.

### Statistical analysis

#### General statistical considerations

All statistical analyses will be performed using SAS® (SAS Institute, Cary, NC, USA).

For efficacy variables, we will use a Full Analysis Set, which will include all randomized subjects with a valid primary efficacy baseline measurement and at least one valid primary efficacy measurement. A robustness evaluation using the Completer Set (CS) will also be performed for the primary efficacy variable. The CS is a subset of the FAS and will include all subjects with a valid measurement at the end of the study Period (15 months) for the primary efficacy variable.

A summary of demographic data and baseline characteristics, as well as medical and procedure history will be presented for the whole population (all treatment groups combined) and for each treatment group. For continuous variables, summary statistics (n [number of available measurements], arithmetic mean, standard deviation [SD], median, interquartiles, minimum, and maximum) will be tabulated. For descriptive statistics of continuous variables, change from baseline and each time point will be displayed.

Frequency tables (frequency counts and percentages) will be presented for categorical data.

#### Primary outcome

The outcome of interest is the probability of remission achievement (rate of remission) of the index episode at 15 months post inclusion. Time to remission is defined as the number of days between the date of inclusion and remission or the last follow-up visit in case of no remission (maximum duration: 15 months). But the exact time of this event will not be known (the event could occur during the interval of two visits), so we will use methods for the analysis of interval-censored data. For calculation, all patient lost to follow-up will be considered as not in remission. A Cox proportional hazard model will be used to assess the impact of the intervention (Effect size). Covariates could be added in the Cox’s proportional hazards regression model if both groups cannot be compared on baseline characteristics alone. The adjusted hazard ratios and their 95 % confidence interval will be reported.

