### Objective and research questions

Primary objective:

The main objective is to compare the effectiveness (rate of remission of index episode at 15 months post inclusion, without relapse during follow-up) of the add-on ENVIE psychoeducational program vs. regular treatment only, in unipolar non-chronic (<2 years) outpatients with moderate to severe depression, without psychotic features.

Secondary objectives:

Comparing add-on psychoeducational program with treatment as usual in regards to:Decrease in depression intensity between inclusion and at 3, 6, 9 and 15 months post inclusion;Response rate 15 months after inclusion;Relapse rate 15 months after inclusion;Hospitalization rate during the follow-up period;Treatment adherence (antidepressants) between inclusion and at 3, 6, 9 and 15 months after inclusion;Changes in quality of life and global functioning between inclusion and at 9 and 15 months after inclusion;Modification of psychotropic treatments between inclusion and at 15 months post inclusion.

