### Sample size

For the control group the full remission rate at 15 months is expected to be 30 % [48]. If, in the experimental group, this rate is 15 % higher, with a power of 0.80 and a two-tailed significance level at 0.05, the sample size ends up to 166 patients per group. Because loss to follow-up will be considered as “not in remission”, no adjusted sample size for taking dropouts into account has to be established. Thus, a total number of 332 subjects will be enrolled in the study. Each center will recruit between 20 and 40 patients: one to 2 psychoeducational groups of 8–10 patients and 10–20 patients in the control group.

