#### Secondary outcomes

The rate of response (decrease of MADRS score by 50 %), and rate of relapse (MADRS >12 after remission of the index episode) at 15 months after inclusion will be analyzed with the similar method used for the main criterion.

A mixed-model will be used to analyze:Variations (intra- and between-group) of depression intensity using MADRS and BDI scores between inclusion, and at 3, 6, 9 and 15 months after inclusion.And model the evolution of MADRS and BDI scores during follow-upVariations (intra- and between-group) of global functioning (using the FAST) between inclusion, and at 9 and 15 months after inclusion,Variations of quality of life using WHOQOL-26 scale between inclusion, and at 9 and 15 months after inclusion,

The rate of relapse (MADRS >12 after remission of the index episode) at 15 months after inclusion, the rate of hospitalization during follow-up and the discontinuation rate of antidepressant therapy at 15 months after inclusion will be analyzed using a chi-square test or Fisher’s exact test if the chi-square is not valid.

The between-group comparison on variation in treatment adherence using MARS and changes in benzodiazepines doses between inclusion and 15 months post inclusion will be performed using the student-t test if distribution is normal or the Mann–Whitney test, if otherwise.

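### The primary endpoint is relapse-free remission at 15 months, but the stated primary test is a Cox model of time to remission that does not mention relapse

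*Protocol article*

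**What the plan says.** - **Objective and research questions:** the effectiveness measure is the "rate of remission of index episode at 15 months post inclusion, without relapse during follow-up".
- **Primary endpoint:** remission is a MADRS "score ≤ 12 for over 8-weeks, without relapse during the follow-up period". The Abstract agrees.
- **Sample size:** "For the control group the full remission rate at 15 months is expected to be 30" per cent, against a rate 15 points higher in the experimental group, with 80% power at two-sided 5%. This gives 166 per group. Losses count as non-remission, so the number is not inflated.
- **Primary outcome (statistical analysis):** the section opens by naming the 15-month remission rate as the outcome of interest. It then sets the analysed variable: "Time to remission is defined as the number of days between the date of inclusion and remission", or to the last follow-up visit when there is no remission. Interval-censored methods are to be used, and "A Cox proportional hazard model will be used to assess the impact of the intervention (Effect size"). Hazard ratios with 95% CIs are to be reported. The section does not mention relapse and gives no comparison of the 15-month proportions.
- **Secondary endpoints and Secondary outcomes:** relapse (MADRS above 12 once the index episode has remitted) is a separate endpoint. Response and relapse at 15 months "will be analyzed with the similar method used for the main criterion". Relapse is also listed for a chi-square or Fisher test.

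**The concern.** The endpoint is a status that can be judged only at the end of follow-up. The analysed variable is the time at which something happens during follow-up. Once a Cox model records an event, what happens to that patient afterwards no longer enters. Take a patient who remits by month 3 and relapses by month 9: on the wording of the Primary outcome section this is an event, and on the Primary endpoint section it is a failure.

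This matters because relapse is prominent in the trial's rationale. The Background cites relapse in up to 85% of patients and names poor adherence and low self-efficacy as recurrence factors that psychoeducation targets. One ENVIE session teaches recognition of early signs of relapse. If the programme worked mainly by keeping remitted patients well, a time-to-remission test could miss it. If it brought earlier or more frequent remission that did not last, the same test could declare success although the stated endpoint did not differ.

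**Working it through.** **1. The plan's own figure.** Inputs from Sample size: p1 = 0.30, p2 = 0.45, two-sided 5%, power 80%; 1:1 allocation from Eligibility assessment and randomization. With the pooled-variance formula and mean proportion 0.375:

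n = [1.960·√(2·0.375·0.625) + 0.842·√(0.30·0.70 + 0.45·0.55)]² / 0.15² = (1.342 + 0.569)² / 0.0225 ≈ 162.3, so 163 per group.

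This is within 2% of the stated 166. Power at 166 per group is Φ[(0.15·√166 − 1.342)/0.676] = Φ(0.873) = 80.9%.

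**2. Does the figure show which test was meant?** No. Under proportional hazards the same rates give HR = ln(0.55)/ln(0.70) = 1.676. Freedman's formula needs 123 events, and 123/(0.30 + 0.45) = 164 per group. The stated 166 is compatible with either analysis.

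**3. What the face-value test detects.** The article gives no first-remission or relapse rates, so those below are assumptions. Relapse-free remission is the cumulative remission probability times (1 − relapse probability among remitters). Simulations use 166 per arm and visits at 3, 6, 9 and 15 months. In rows (a) and (b) the control arm's cumulative remission is 20/35/45/55% at those visits.

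| Scenario | Remission by 15 months, control vs ENVIE | Implied relapse among remitters | Endpoint | Time-to-remission test rejects | Proportion test rejects |
|---|---|---|---|---|---|
| (a) fewer relapses only | 55% vs 55% | 45% vs 18% | 30% vs 45% | 5% | 80–82% |
| (b) more remissions, not sustained | 55% vs 67% | 45% vs 55% | 30% vs 30% | 59–66% | 4–5% |
| (c) mixed | 40% vs 48% | 25% vs 6% | 30% vs 45% | 31–32% | 81–82% |
| (d) no relapse, proportional hazards | 30% vs 45% | none | 30% vs 45% | 82% | 82% |

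Implied relapse is 1 − endpoint/remission, for example 1 − 0.30/0.55 = 45%. The ranges cover repeated simulations. In (b) the result also depends on how the extra remissions are spread over the visits: 59% when the control curve is scaled up, a few points more under proportional hazards.

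**4. A check by formula.** With remission 50% vs 60% and relapse 40% vs 25%, the endpoint is 0.50·0.60 = 30% vs 0.60·0.75 = 45%. HR = ln(0.40)/ln(0.50) = 1.322, expected events = 166·(0.50 + 0.60) = 182.6, and Cox power = Φ(0.279·√182.6/2 − 1.960) ≈ 47%, against 81% for proportions.

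The difference can also go the other way. With remission 60% vs 75% and relapse 50% vs 40%, the endpoint is again 30% vs 45%, and Cox power is 87%.

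**5. The other reading of the event.** Suppose the event is remission never followed by relapse, dated at remission, and everyone else stays event-free to 15 months. If relapse is independent of remission time, the log-rank test rejects 79–80% in (a), 4–5% in (b) and 81% in (c), in line with the proportion test. However, whether a month-3 event exists is then settled only by follow-up to month 15. The risk sets use future information, and the hazard ratio loses its usual meaning.

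**The case against.** The strongest reply is that the Primary outcome section never says first remission. It opens with the 15-month rate, which the article elsewhere defines as relapse-free, so the Cox event could be that endpoint. This has force: on that reading the rejection rates are restored (step 5). It does not rescue the reported quantity, because the planned effect measure is a hazard ratio whose events are defined by the future. The Secondary endpoints section also treats relapse as something that follows remission, so remission on its own does not exclude later relapse. The event is therefore either mismatched with the endpoint or unsuited to the model.

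Several stronger inferences are tempting, and the article does not support them:

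- **That the sample size proves a two-proportion test was intended.** It does not (step 2). The Sample size section also speaks of full remission without repeating the no-relapse condition.
- **That a relapse benefit would be lost to the trial.** Relapse is a secondary endpoint with a stated chi-square or Fisher test. A secondary result cannot, however, stand in for part of the primary endpoint.
- **That response has the same defect.** Response carries no relapse condition. The question there is only whether status at 15 months or first attainment is analysed.
- **That the scenarios predict this trial.** They are selected illustrations, and (b) has more relapse under the programme, contrary to its rationale.

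Nor is this detail that can be left to an analysis plan: the article itself fixes the variable, the model and the effect measure.

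**Conclusion.** The concern holds as a mismatch between the primary endpoint and the primary analysis. It is not an error in the sample size. At face value the test counts patients as events whom the endpoint counts as failures; on the alternative reading the hazard ratio has no clear meaning. A reader might conclude that the plan definitely tests time to first remission and cannot answer the trial's question. That goes too far, since the word first is absent and the alternative reading keeps a usable between-arm test.

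Under the assumed rates, the face-value test ranges from about 5% power for the planned 30% vs 45% difference to about 60% rejection when the endpoint is equal in both arms. With no relapse and proportional hazards the two analyses agree. The size of the discrepancy depends on first-remission and relapse rates that the article does not give; the mismatch in the text does not.

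**What to change.** Make the primary test the between-arm comparison of the proportion in remission at 15 months without relapse. Count losses as non-remission, as the article already states. Report a risk difference with 95% CI, adjusted for centre because randomisation is stratified by centre. Keep the interval-censored time-to-remission model as a secondary analysis, and state what its event is and how later relapse is handled.

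As a separate and smaller point, response is defined at 15 months and should also be compared as a 15-month proportion.

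The cost is wording in the protocol and analysis plan. No new data are needed, and 166 per group gives 80.9% power for the unadjusted comparison. The choice of analysis set and any adjustment for baseline MADRS are separate matters that this change does not require.

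### Covariates enter the primary Cox model only if the arms look unequal at baseline, so the adjusted hazard ratio that the plan promises is not defined before the data are seen

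*Protocol article*

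**What the plan says.** All references are to the protocol article.

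- **Statistical analysis, Primary outcome.** Remission is analysed with a Cox model in an interval-censored setting. Covariates are optional and may be added to the "regression model if both groups cannot be compared on baseline characteristics alone". The sentence is awkward, but its only sensible meaning is that adjustment depends on observed baseline imbalance. No covariates, test or threshold are named. The next sentence begins "The adjusted hazard ratios and their 95" and promises the interval, as if adjustment were certain.
- **Eligibility assessment and randomization.** The permuted-block list has "varying block sizes and will be stratified in participating centers". The Design section gives 11 centres. Baseline MADRS is measured at the first visit.
- **Sample size.** In controls, "the full remission rate at 15 months is expected to be 30" per cent, and the program is assumed to add 15 points. Planning for 80% power in a two-sided 5% test, the article concludes that "the sample size ends up to 166 patients per group". It makes no allowance for attrition.
- **Secondary outcomes.** Response and relapse are to be analysed much as the primary outcome is, so the rule carries over to them. Relapse is also listed under chi-square or Fisher tests.

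**The concern.** Two sentences in the same paragraph do not fit together. One makes adjustment optional and dependent on the data; the next takes an adjusted estimate for granted. A reader cannot tell which hazard ratio is the primary result.

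The trigger is also the wrong criterion. Under random allocation, a covariate that differs between arms does so by chance, and the difference says nothing about whether the covariate predicts remission. Two covariates have a claim that does not depend on imbalance:

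- **Centre** is the randomisation stratum. Stratification keeps the arms close to balanced within centre, so an imbalance trigger would hardly ever select it.
- **Baseline MADRS** plausibly predicts an endpoint defined by an absolute MADRS threshold. Entry requires a score above 24 and remission requires 12 or less. A patient entering at 25 must fall 13 points; one entering at 40 must fall 28.

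At stake are a primary estimate fixed in advance and some power, in a design with little to spare.

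**Working it through.** **1. The plan's own sample size.** Inputs from the Sample size section: 0.30 against 0.45, two-sided 0.05, power 0.80. Pooled-variance formula without continuity correction:

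n = [1.96·√(2·0.375·0.625) + 0.8416·√(0.30·0.70 + 0.45·0.55)]² / 0.15² = (1.342 + 0.569)² / 0.0225 ≈ 162.3, so 163 per group.

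The stated 166 is within 3 per group of this and has power 80.9%. The figure reproduces, and it assumes no covariates.

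**2. The same design as time to event.** Under proportional hazards, HR = ln(0.55)/ln(0.70) = 1.68 (log-HR 0.516). Expected remissions are 166 × (0.30 + 0.45) = 124.5. Schoenfeld's formula needs 118 events; power with 124 events is 82.0%.

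**3. What the conditional rule does.** A grouped proportional-hazards (complementary log-log) model was simulated on the visits at 3, 6, 9 and 15 months, with 332 patients, 11 centres, allocation balanced within centre, and 2,000 runs per setting. These inputs are assumptions, not in the documents:

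- the prognostic strengths: log-HR per SD of baseline MADRS and between-centre SD, both 0.3 (weaker) or both 0.5 (stronger);
- seven screened variables, namely baseline MADRS and six unrelated to outcome;
- a trigger of p < 0.05 on each variable;
- a constant hazard and no dropout.

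The prespecified model used baseline MADRS and centre indicators. The value 1.68 was the covariate-conditional hazard ratio.

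| Model | Power, weaker | Power, stronger | Type I, weaker | Type I, stronger |
|---|---|---|---|---|
| Unadjusted | 78.3% | 71.5% | 4.9% | 4.4% |
| Conditional rule | 78.2% | 71.7% | 4.6% | 4.2% |
| Prespecified | 81.1% | 81.1% | 5.5% | 5.4% |
| Most favourable of the three | – | – | 6.2% | 6.5% |

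Monte Carlo error on the type I rates is √(0.05·0.95/2000) ≈ 0.5 points.

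- **Trigger.** Adjustment was used in about 30% of trials, matching 1 − 0.95⁷ = 0.302. It was chance alone, since allocation was random.
- **Power.** Prespecified minus conditional is 81.1 − 78.2 = 2.9 points in the weaker setting and 81.1 − 71.7 = 9.4 in the stronger. The rule gained essentially nothing over no adjustment.
- **Mechanism.** In the weaker setting the mean SE of the log-HR was 0.185 unadjusted and 0.187 prespecified, while the mean log-HR was 0.502 and 0.534. The difference in power comes from the estimate, not its standard error. In the stronger setting the unadjusted mean was 0.468 against the true 0.516, that is, HR 1.60 against 1.68.

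**Limits of the check.** In the weaker setting the prespecified model overshot slightly (0.534 against 0.516) and its type I error was 5.5%, so part of the 3-point gain may be small-sample behaviour of the centre indicators. The rule's failure to recover power partly reflects that six of the seven screened variables were noise. One prespecified fit in 2,000 failed to converge in the stronger setting; that mean log-HR is not used, and the rejection rates are unaffected.

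**The case against.** The strongest reply is that this is a condensed article and that the covariate list and the handling of centre belong in an analysis plan that is not shown. That is right as far as omissions go. The article does not say that centre or baseline MADRS will be left out, and a reader should not infer that they are. But the article does not merely stay silent: it states a data-dependent rule and calls the result adjusted. An analysis plan that fixed the covariates would have to override that text.

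Other stronger readings are tempting and are not supported:

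- **Lost precision or wrong standard errors.** In a Cox model the loss is one of power through attenuation of the hazard ratio; the standard errors above barely move. Ignoring the stratum tends to make the test conservative. Power gains computed by dividing n by (1 − R²) use a linear-model formula that does not fit this analysis.
- **Inflated type I error.** Applied strictly, the rule gave 4.6% and 4.2%. The 6.2% and 6.5% arise only if the most favourable model is picked, which the article does not say will be done. The optional wording merely leaves room for it.
- **More than an even chance of triggering.** Fifteen independent tests at 5% give 1 − 0.95¹⁵ = 54%, but the article plans only descriptive baseline tables and names no test, and MADRS and BDI measure the same thing. Any such figure is illustrative.

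It is also fair that restricting entry to MADRS above 24 may weaken its prognostic value. The documents do not settle that.

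**Conclusion.** The point holds in this form: the rule for the primary model is badly fixed and is inconsistent with the promise of an adjusted hazard ratio. That conclusion rests on the text alone.

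The size of the power loss does not. About 3 to 10 points is an illustrative range under assumed prognostic strengths, and the lower end should be read loosely. If centre and baseline MADRS predict remission only weakly, the gain could be smaller still. The stated 166 per group is unaffected, and no bias or type I error inflation is shown for the rule as written. This is a nearly free improvement, not a threat to the trial's validity.

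**What to change.** In the Primary outcome section:

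1. Delete the sentence that ties covariates to baseline comparability.
2. Prespecify the primary Cox model as treatment plus baseline MADRS, with centre as a stratification factor, whatever the observed balance. State one form, either a stratified Cox model or a random centre effect, before anyone sees data by arm. With about 332/11 ≈ 30 patients and 124.5/11 ≈ 11 expected remissions per centre, the choice deserves thought and should not be left open.
3. Define the reported adjusted hazard ratio as the one from this model. Give the unadjusted hazard ratio as supportive and label any other adjustment as sensitivity analysis.
4. Apply the same covariates to the response analysis, to any relapse analysis that uses the primary method, and to the mixed models where suitable. Do not extend them to the chi-square or Fisher comparisons, or to the t or Mann–Whitney comparisons, which take no covariates.

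The cost is wording in the protocol or analysis plan. Centre and baseline MADRS are already recorded, and the sample size stays as it is.
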